## 1. OBJECTIVES

Primary Objective:

The aim of the present study is to determine the effect of probiotics in high-risk infants on the prevalence and severity of asthma and allergic rhinitis, lung function and specific IgE at the age of 5 or 6 years.

## **2. STUDY DESIGN**

A randomised double-blind placebo-controlled prospective study was carried out in 156 high-risk children. 98 children completed the intervention period and the two years of follow-up. The present study comprises a follow-up at the age of 5 or 6 years, in the outpatient clinic.

### 3. STUDY POPULATION

- 3.1 **Population (base):** Children who previously participated in the PANDA study
- 3.2 **Inclusion criteria:** Children who previously participated in the PANDA study
- 3.3 **Exclusion criteria:** None
- 3.4 **Sample size calculation:** We will try to get as little as possible loss to follow-up by trying to find all the former participants of the PANDA-study and to ask for the collaboration.

For the pilot study evaluating the diagnostic value of measurement of nasal nitric oxide, we will evaluate the complete cohort, not considering whether the child has received probiotics. We estimate the prevalence of allergic rhinitis to be 15% in this cohort. To be able to detect a statistical significant difference between nasal NO in the subjects with a diagnosis of allergic rhinitis from the questionnaire and subjects who do not, we will need a minimum of 10-15 participants with allergic rhinitis, and the same amount who do not suffer from allergic rhinitis. In evaluating this, we consider the means for NO in both groups to be 450 and 600 ppb, the standard deviation 115 ppb, the power 90% and the alfa 0.05. With the expected prevalence of allergic rhinitis (14 of 95 participants), this should be possible.

#### **4. TREATMENT OF SUBJECTS**

Not applicable

## 5. INVESTIGATIONAL MEDICINAL PRODUCT

Not applicable

## 6. METHODS

### 6.1 Study parameters/endpoints

#### 6.1.1 Main study parameter/endpoint

The prevalence of allergic disease, focussing on the prevalence of asthma and allergic rhinitis.

Definition of asthma: Periodic wheezing and dyspnoea, combined with a 9% reversibility in FEV1 and/or exhaled NO above 20 ppb.

Definition of allergic rhinitis: Periodic or perennial sneezing, runny, or blocked nose when not having a cold or the flu.

#### 6.1.2 Secondary study parameters/endpoints (if applicable)

Specific IgE to allergens.

#### 6.1.3 Other study parameters (if applicable)

Not applicable.

### 6.2 Randomisation, blinding and treatment allocation

The previous study was double-blinded, this was abated at the end of the PANDA study. In this follow-up study, the researcher will be blinded, but parents are not.

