## SUMMARY

**Rationale:** Probiotics, if instituted early in life, can give a significant reduction of development of eczema in infants at high risk of atopic diseases. In 2004 a randomized controlled trial started to investigate whether probiotics have a significant effect on the development of atopic symptoms as eczema, allergic rhinitis, food allergy and asthma. This study population has been followed until the age of two years. The present study is meant as a prolongation of the former study, we will perform a follow-up study of the included children on development of atopic diseases, in particular asthma and allergic rhinitis.

**Objective:** To establish the effect of perinatal probiotics on the prevalence of allergic disease at the age of 5 years.

**Study design:** Prospective, single blind, randomised, placebo-controlled trial.

**Study population:** Subjects are 98 predominantly Caucasian high risk children, having either a mother, or both a father and at least one sibling with past or present atopic diseases, to whom probiotics or placebo was administered perinatally during the previously carried out PANDA study.

**Intervention (if applicable):** None.

**Main study parameters/endpoints:** Development of allergic symptoms, evaluated by questionnaire and physical examination. Development of allergic asthma and allergic rhinitis, measured by lung function testing, nitric oxide measurements in exhaled air, and specific IgE to allergens.

**Nature and extent of the burden and risks associated with participation, benefit and group relatedness:** Parents and child are asked to fill in a questionnaire, and pay one visit to the out patient department for physical examination, blood sampling and pulmonary function testing with measurement of exhaled nitric oxide. The risks of these procedures are negligible and the burden minimal. It should be carried out specifically in these children, since they have been included in the former study and received placebo or probiotics.

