### 6.3 Study procedures

The questionnaire is based on the ISAAC questionnaire. It will be used to evaluate the participants for symptoms indicative of asthma, allergic rhinitis, eczema and food allergy at the age of 5 or 6 years, with the most used and best comparable questionnaire of nowadays research in allergy.

The treating physician will be asked for doctor-diagnosed atopic diseases (asthma, allergic rhinitis, food allergy, eczema, urticaria).

Physical examination.

Baseline pulmonary function (forced expiratory volume in 1 second (FEV1), forced vital capacity (FVC), peak expiratory flow (PEF), and subdivisions of forced expiratory flow) will be measured. Airway reversibility will be measured after administration of 400 microgram of salbutamol. Exhaled nitric oxide will be measured, including nasal nitric oxide (nNO). nNO will be measured during breath holding (nNO-BH) and during humming (nNO-HE). nNO-measurement is not experienced as invasive by the child. nNO-BH is measured during breath hold after inhalation to TLC. The subjects will be asked to hold their breath for 10 seconds while air is sampled from the right nostril.

To measure nNO-HE, subjects will be asked to make a humming noise during nasal exhalation at the frequency of a tuning fork. Before nNO-HE measurements subjects are asked not to speak during 5 minutes. After inhalation of ambient air to TLC subjects exhale to FRC through their left nostril, while air is sampled from the right.

The nasal humming procedure will be done at two different frequencies with the assistance of tuning forks of respectively 128 and 440 Hz (nNO-HE128 and nNO-HE440, respectively).

Participants will be asked to stop the possible use of nasal corticosteroids for 6 weeks before nNO-measurement, long acting  $\beta$ -mimetica for 48 hours before lung function testing, and short acting  $\beta$ -mimetica for 12 hours before lung function testing, if clinically acceptable for the medical situation of the child. This will be evaluated by the investigator and deliberated with the treating physician.

Specific IgE will be determined by Phadiatop assay, concerning the most common allergens, in 1 ml. of blood.

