### **9.2 Recruitment and consent**

Subjects will be recruited by [name] among the participants of the previous PANDA-study. Parents will be asked if their child is willing to participate. They will receive printed information and will be contacted by phone after one week by the investigator. If they decide to participate, they are asked to return the informed consent form attached to the printed information.

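### Unblinded parents supply all of the rhinitis definition and a necessary part of the asthma definition, so differential reporting can bias the main relative risks and blinding the researcher does not prevent it

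*Protocol*

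**What the plan says.** **Blinding.** On the earlier trial, Protocol section 6.2 states: "The previous study was double-blinded, this was abated at the end of the PANDA study". On the present study it states: "In this follow-up study, the researcher will be blinded, but parents are not". The Summary describes the design as "Prospective, single blind, randomised, placebo-controlled trial".

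**Main endpoint (6.1.1).** "The prevalence of allergic disease, focussing on the prevalence of asthma and allergic rhinitis". Asthma is "Periodic wheezing and dyspnoea, combined with a 9% reversibility in FEV1 and/or exhaled NO above 20 ppb". Allergic rhinitis is "Periodic or perennial sneezing, runny, or blocked nose when not having a cold or the flu".

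**Source of the symptoms.** Section 6.3 says of the ISAAC-based questionnaire: "It will be used to evaluate the participants for symptoms indicative of asthma, allergic rhinitis, eczema and food allergy". The Summary has parents and child completing it, and section 3.4 speaks of a rhinitis diagnosis taken from it.

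**Other data collected (6.3).** Physician-diagnosed atopic disease, physical examination, lung function with reversibility, exhaled and nasal NO, and specific IgE. Section 6.1.2 makes specific IgE a secondary endpoint.

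**Analysis (8.1).** Relative risks with 95% confidence intervals for the main endpoint.

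**Contact with parents (9.2).** "They will receive printed information and will be contacted by phone after one week by the investigator".

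**The concern.** Blinding the researcher protects what the researcher measures or judges. Here the decisive input to the main endpoint comes from people who know which product the child received. If parents in one arm report nasal or chest symptoms more readily than parents in the other, the relative risk moves away from 1 with no biological effect, and the planned interval cannot tell the two apart.

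Two features add to this. The Summary says allergic asthma and allergic rhinitis are measured with lung function, exhaled NO and specific IgE, but the rhinitis definition in 6.1.1 uses none of these, so the objective check that the Summary implies is missing from the operative definition. In addition, the protocol text contains no step that asks parents to keep the allocation from the researcher, fixes the order of data collection or records a disclosure.

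**Working it through.** **1. How far each diagnosis depends on parental report.**

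- Rhinitis: symptoms only, taken from the questionnaire. Nothing in the definition limits the effect of reporting.
- Asthma: symptoms AND (reversibility and/or exhaled NO). Symptoms are necessary but not sufficient. Over-reporting can add only children who meet an objective criterion, and under-reporting can remove any true case.

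**2. Effect on the expected RR with no true effect.** Let p be the true prevalence in both arms, and let r be the probability that a symptomatic child is reported as such in the probiotic arm relative to the placebo arm.

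- Rhinitis: RR = (p × r) / p = r.
- Asthma, if a share q of reported symptomatic children meets the objective criterion in both arms: RR = (p × r × q) / (p × q) = r. For p = 0.15, r = 0.80, q = 0.50: 0.060 / 0.075 = 0.80.

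So 20%, 30% or 50% relative under-reporting gives an RR of 0.80, 0.70 or 0.50. The objective criterion reduces the number of children affected, but does not by itself remove bias from the ratio.

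**3. Inputs for the interval.** The protocol gives no sample-size figure for the probiotic comparison, so there is none to reproduce. Its only one, 10 to 15 per group for the nasal NO pilot, does not bear on this point. From the documents: 98 children completed the two-year follow-up (section 2), and expected rhinitis prevalence is 15% (section 3.4; 14/95 = 14.7%). Assumed: an equal split, 98/2 = 49 per arm, and the reported prevalences below.

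**4. Chance that the planned interval excludes 1.** With i of n cases in the probiotic arm and j of n in the placebo arm, the log-method interval excludes 1 when |ln(i/j)| > 1.96 × √(1/i − 1/n + 1/j − 1/n). Summing the exact binomial probabilities over all such pairs, with n = 49:

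| Reported, probiotic vs placebo | Expected RR | Interval excludes 1 |
|---|---|---|
| 15% vs 15% (no bias) | 1.00 | 3.4% |
| 13.5% vs 16.5% | 0.82 | 4.9% |
| 12% vs 15% | 0.80 | 4.6% |
| 10.5% vs 15% | 0.70 | 6.5% |
| 7.5% vs 15% | 0.50 | 13.1% |
| 12% vs 20% | 0.60 | 15.2% |

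If all 156 randomised children returned (78 per arm, an upper limit), the no-bias figure is 4.0%, the 13.5% vs 16.5% split gives 6.8%, and 12% vs 20% gives 24.8%.

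**5. Reading.** The point estimate shifts in direct proportion to the reporting ratio. The chance of a falsely significant interval rises clearly only when the bias is large, because the study is small and the condition is uncommon.

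**The case against.** **The label.** A reader might infer that calling the study single blind contradicts section 6.2. It does not: one party is blinded, the other is not, and the protocol says so openly.

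**The core cannot be undone.** Blinding ended with the earlier trial. Asking parents not to disclose protects the assessor and leaves the parents' own reporting as it is. This stands, and it is why the fix needs a second part.

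**Mitigation is already present.** Asthma needs an objective criterion, physicians are asked for diagnoses, specific IgE is a secondary endpoint, and lung function and IgE are in the primary objective (section 1). This is true and limits the concern for asthma. It does not help rhinitis, whose definition draws on none of these.

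**Direction and size.** It is tempting to say that the bias favours probiotics, since the hypothesis is one of prevention and parents of placebo children know they did not receive the active product. The documents do not establish this, and the bias could run the other way. Every split above is an assumption.

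**Broken researcher blinding.** A reader might infer from the telephone call in section 9.2 that assessor blinding will fail. The call is a recruitment contact. The text does not show whether the caller is also the blinded assessor, and the invitation letter is not available. Only the absence of a safeguard in the protocol text can be stated.

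**Conclusion.** The point holds as a weakness of design that can be reduced cheaply. It is neither a contradiction nor proof that a result would be false. Unblinded parents, with the child, supply the whole of one main diagnosis and a necessary part of the other, so the main relative risks are open to differential reporting: fully for rhinitis, and for asthma among children whose diagnosis then turns on reported symptoms.

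Under the assumed 12% versus 20% split the expected RR is 0.60 with no effect, and the planned interval excludes 1 in about 15% of trials at 49 per arm, against 3.4% without bias. Under the milder 13.5% versus 16.5% split the figure is about 5%. These results rest on equal arms, on 98 children attending, on a true prevalence of 15%, and on reporting differences that the documents do not supply. A misleading estimate is plausible with moderate bias, whereas a falsely significant one needs large bias.

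**What to change.** **(a) Sections 6.2 and 6.3, and the invitation.** Ask parents not to reveal the allocation to the researcher. Collect the questionnaire before the visit, and score it by a fixed rule on coded data before the allocation is linked. Record any disclosure. This protects assessor blinding only.

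**(b) Sections 6.1 and 8.1.** Prespecify a supportive analysis that depends less on parental report and uses data already collected:

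- rhinitis symptoms together with positive specific IgE, which also brings section 6.1.1 into line with the Summary;
- physician-diagnosed asthma and rhinitis;
- FEV1 reversibility, exhaled NO and specific IgE by arm.

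Report it beside the main RR, and state in advance that a difference seen only in reported symptoms will be interpreted with caution. An absolute bar on claiming a symptom effect would go too far: with about 98 children the objective measures can differ in direction by chance, and a true effect on symptoms without one on sensitisation would be dismissed. These measures are also not wholly free of parental influence, since section 9.4 makes lung-function testing depend partly on parents' willingness to stop beta-mimetics. Numbers tested should therefore be given by arm.

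The single-blind label needs no correction.

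**Cost.** A sentence in the invitation, a fixed order of collection, a disclosure record and a modest extra analysis, with no new tests or participants. The downside is a more cautious conclusion if only reported symptoms differ.

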### 6.3 Study procedures

The questionnaire is based on the ISAAC questionnaire. It will be used to evaluate the participants for symptoms indicative of asthma, allergic rhinitis, eczema and food allergy at the age of 5 or 6 years, with the most used and best comparable questionnaire of nowadays research in allergy.

The treating physician will be asked for doctor-diagnosed atopic diseases (asthma, allergic rhinitis, food allergy, eczema, urticaria).

Physical examination.

Baseline pulmonary function (forced expiratory volume in 1 second (FEV1), forced vital capacity (FVC), peak expiratory flow (PEF), and subdivisions of forced expiratory flow) will be measured. Airway reversibility will be measured after administration of 400 microgram of salbutamol. Exhaled nitric oxide will be measured, including nasal nitric oxide (nNO). nNO will be measured during breath holding (nNO-BH) and during humming (nNO-HE). nNO-measurement is not experienced as invasive by the child. nNO-BH is measured during breath hold after inhalation to TLC. The subjects will be asked to hold their breath for 10 seconds while air is sampled from the right nostril.

To measure nNO-HE, subjects will be asked to make a humming noise during nasal exhalation at the frequency of a tuning fork. Before nNO-HE measurements subjects are asked not to speak during 5 minutes. After inhalation of ambient air to TLC subjects exhale to FRC through their left nostril, while air is sampled from the right.

The nasal humming procedure will be done at two different frequencies with the assistance of tuning forks of respectively 128 and 440 Hz (nNO-HE128 and nNO-HE440, respectively).

Participants will be asked to stop the possible use of nasal corticosteroids for 6 weeks before nNO-measurement, long acting  $\beta$ -mimetica for 48 hours before lung function testing, and short acting  $\beta$ -mimetica for 12 hours before lung function testing, if clinically acceptable for the medical situation of the child. This will be evaluated by the investigator and deliberated with the treating physician.

Specific IgE will be determined by Phadiatop assay, concerning the most common allergens, in 1 ml. of blood.

#### **6.4 Withdrawal of individual subjects**

Subjects can leave the study at any time for any reason if they wish to do so without any consequences. The investigator can decide to withdraw a subject from the study for urgent medical reasons.

**6.4.1 Specific criteria for withdrawal (if applicable)** Not applicable.

**6.5 Replacement of individual subjects after withdrawal** Not applicable.

**6.6 Follow-up of subjects withdrawn from treatment** Not applicable.

#### **6.7 Premature termination of the study**

No reason to terminate this study prematurely.

## 7. SAFETY REPORTING

### 7.1 Section 10 WMO event

In accordance to section 10, subsection 1, of the WMO, the investigator will inform the subjects and the reviewing accredited METC if anything occurs, on the basis of which it appears that the disadvantages of participation may be significantly greater than was foreseen in the research proposal. The study will be suspended pending further review by the accredited METC, except insofar as suspension would jeopardise the subjects' health. The investigator will take care that all subjects are kept informed.

### 7.2 Adverse and serious adverse events

No serious adverse effects are to be expected, children will undergo physical examination, capillary blood sampling and lung function testing. Mild adverse effects could be dyspnoea or wheezing during the 2 days before the lung function testing, for which the investigator will provide good accessibility for deliberations of the parents. Another mild adverse effect could be exacerbation of allergic rhinitis since intranasal corticosteroids will be stopped during 6 weeks before testing. For this, the investigator can be contacted. Restarting the medication is possible at any time by the child, parents or treating physician and discontinuation of the medication can be rejected at any time by the child, parents or treating physician.

Adverse events are defined as any undesirable experience occurring to a subject during a clinical trial, whether or not considered related to the investigational drug. All adverse events reported spontaneously by the subject or observed by the investigator or his staff will be recorded.

A serious adverse event is any untoward medical occurrence or effect that at any dose results in death;

- is life threatening (at the time of the event);
- requires hospitalisation or prolongation of existing inpatients' hospitalisation;
- results in persistent or significant disability or incapacity;
- is a congenital anomaly or birth defect;
- is a new event of the trial likely to affect the safety of the subjects, such as an unexpected outcome of an adverse reaction, lack of efficacy of an IMP used for the treatment of a life threatening disease, major safety finding from a newly completed animal study, etc.

All SAEs will be reported to the accredited METC that approved the protocol, according to the requirements of that METC.

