### **9.4 Benefits and risks assessment, group relatedness**

No direct benefit can be expected for the participants, except for a thorough screening for the presence of atopic diseases with if indicated an appropriate reference to a specialist. The risk of blood sampling is negligible, and the same applies to pulmonary function testing including exhaled nitric oxide measurement. For the need of stopping the inhaled beta-mimetics, a risk of dyspnoea and wheezing exists, which will be treated with re-administration of beta-mimetics. The same applies to discontinuation of nasal corticosteroids, which carries the risk of exacerbation of allergic rhinitis. If the condition of the child does not allow stopping the above mentioned medication or the parents are not willing to do so, they can still fulfill the questionnaires but they cannot perform lungfunction testing in case of beta-mimetics, or nasal NO measurement in case of nasal corticosteroids.

We are convinced that the yield of the study for addressing the effect of probiotics on the development of atopic disease exceeds the burden of one visit to the hospital with the above mentioned diagnostic procedures and the risks.

This follow-up study can only be carried out on these subjects, since they have participated in the primary intervention (the PANDA-study) with either probiotics or placebo.

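### Adverse events are recorded passively although the foreseen mild harms arise during study-requested medication stops, and no stated step asks about symptoms during the stop, restart or last dose

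*Protocol*

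**What the plan says.** Section 6.3 asks participants to stop nasal corticosteroids for 6 weeks before nasal NO (nNO) measurement, long-acting beta-mimetics for 48 hours before lung function testing and short-acting ones for 12 hours, if clinically acceptable. On acceptability it says: "This will be evaluated by the investigator and deliberated with the treating physician".

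Section 7.2 names the harms that may follow. One is respiratory: "Mild adverse effects could be dyspnoea or wheezing during the 2 days before the lung function testing". The other is nasal: "Another mild adverse effect could be exacerbation of allergic rhinitis since intranasal corticosteroids will be stopped during 6 weeks before testing". It offers contact with the investigator for both, and it leaves the way back onto treatment open: "Restarting the medication is possible at any time by the child, parents or treating physician". Its recording rule is: "All adverse events reported spontaneously by the subject or observed by the investigator or his staff will be recorded".

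Section 9.4 says of the dyspnoea and wheezing that they are a risk "which will be treated with re-administration of beta-mimetics", and adds: "The same applies to discontinuation of nasal corticosteroids". It also sets a consequence for children whose condition does not allow a stop or whose parents decline one: they can complete the questionnaires, but "they cannot perform lungfunction testing in case of beta-mimetics, or nasal NO measurement in case of nasal corticosteroids".

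The Summary describes one outpatient visit. Section 6.3 also provides an ISAAC-based questionnaire on symptoms of asthma, rhinitis, eczema and food allergy at age 5 or 6, and a physical examination.

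**The concern.** The study creates the exposure (a medication stop), foresees the harm, and lets the family treat it without involving the study. The recording rule then waits for the family to volunteer the event or for staff to see it. Staff cannot directly observe what happened in the days or weeks before the visit. A short episode settled by restarting the medicine is also the kind of event a family is least likely to mention unasked.

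Two things are at stake. Mild harms of study-requested stops in 5- to 6-year-olds may be under-recorded. And a child who stopped and then restarted may be tested on medication, so that a reading section 9.4 appears meant to exclude enters FEV1 reversibility or nNO.

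**Working it through.** The core of the point is textual, so the provisions are set side by side first. The arithmetic that follows prices the fix and does not measure the problem.

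**Tracing one child through the text**

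1. The investigator and treating physician agree to a stop (6.3). The study should therefore know which children were asked to stop.
2. Symptoms appear during the stop and before the visit (7.2). That this happens at home is a fair inference, not a statement in the protocol.
3. The medicine is restarted (7.2, 9.4). Neither section requires anyone to report this.
4. The child attends the visit. The questionnaire asks about symptoms, but 6.3 ties it to disease at age 5 or 6. Its recall period, its order relative to the tests and any link to adverse event recording are not stated.
5. The bar in 9.4 literally covers children who cannot stop or whose parents will not. It can reasonably be read to include a child who restarted, but no stated step identifies that child.

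**Reach into the asthma endpoint.** Section 6.1.1 requires symptoms plus 9% reversibility in FEV1 and/or exhaled NO above 20 ppb. An undetected beta-mimetic dose that blunts reversibility therefore changes the classification only in a child with symptoms whose exhaled NO is not above 20 ppb.

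**Price of the fix for nNO.** Inputs from section 3.4: means 450 and 600 ppb, SD 115 ppb, alpha 0.05 (taken as two-sided), and 14 expected rhinitis cases among 95 participants, so 95 − 14 = 81 non-cases. Method: two-sample t-test with equal variances. Standardised difference 150/115 = 1.304; noncentrality = 1.304/√(1/n₁ + 1/n₂); degrees of freedom n₁ + n₂ − 2.

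The plan's own figure comes first. Section 3.4 asks for 10 to 15 per group at 90% power. With 14 per group the noncentrality is 3.45 and power is 91.3%; with 13 per group power is 89.1%. The stated range therefore contains the required 14, although 10 per group would give only 78.8%.

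Next, suppose every lost reading comes from a case, while the non-cases stay as shown:

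| Cases v non-cases measured | Noncentrality | Power |
|---|---|---|
| 14 v 81 | 4.51 | 99.4% |
| 10 v 81 | 3.89 | 97.1% |
| 7 v 81 | 3.31 | 90.6% |
| 6 v 81 | 3.08 | 86.2% |
| 8 v 60 (60 is an assumption) | 3.47 | 92.7% |
| 7 v 60 (60 is an assumption) | 3.27 | 89.6% |

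The comparison of means can lose 14 − 7 = 7 case readings and keep 90% power if all 81 non-cases are measured, or 14 − 8 = 6 if only 60 are.

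Section 8.1 plans sensitivity, which is estimated from the cases alone. For a given true sensitivity its standard error is proportional to 1/√(cases), so going from 14 to 7 cases multiplies it by √(14/7) = 1.41.

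**The case against.** The strongest reply is that recording spontaneous reports and staff observations is a coherent rule for a one-visit follow-up without intervention, and that asking actively about mild events is a matter of preference. Much is also in place already: a clinical check before each stop, investigator contact for both foreseen harms, freedom to refuse or restart, follow-up of all adverse events under 7.3, and a bar on testing in 9.4 that presupposes known medication status. The questionnaire form is not shown, and families also receive printed information and a telephone call (9.2). Any of these could carry a last-dose question or an instruction to report.

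Most of this stands, and it limits the point. Only the visible protocol text can be said to lack the step. The child's protection does not depend on it, because treatment can be restarted at any time. What remains is that the pre-stop check covers the decision and not what follows, that a contact route relies on the family using it, and that 9.4 needs information the protocol does not say how to obtain.

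A reader might infer three stronger claims, and the documents support none of them:

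- *The visit asks nothing about symptoms.* The questionnaire in 6.3 asks about asthma and rhinitis symptoms; what is not stated is that it covers the stop period.
- *The probiotic comparison is biased.* Nothing in the protocol suggests that undetected restarts would differ between arms, and the 6.1.1 definition narrows any effect on asthma.
- *The power figures show damage.* They describe only what the pilot could afford to lose.

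**Conclusion.** The point holds as a low-severity improvement to a stated rule. Section 7.2 captures the foreseen harms of the study's own medication stops only if a family volunteers them or staff happen to notice, and no stated step asks about symptoms during the stop, restart or last dose. A treated mild episode can therefore go unrecorded, and the reading it compromises can be taken.

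The size is unknown. The protocol gives neither the number of children using these medicines nor a restart rate, so no event count can be derived and no bias is demonstrated. The conclusion rests on the visible protocol text and on the inference that the events occur away from staff. The power figures rest on the section 3.4 inputs, a two-sided test, and losses confined to rhinitis cases.

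**What to change.** Amend section 7.2: at the existing visit, before testing, staff ask each family that was asked to stop medication about symptoms since stopping, any restart, and the date and time of the last dose. Symptoms are recorded as adverse events.

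Add to section 9.4 that its bar also applies to a child who restarted within the washout window: no lung function test after beta-mimetics, no nNO measurement after nasal corticosteroids, and the questionnaire still completed.

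As an editorial matter only, align the sentence in 7.3 that expects no adverse events with the harms foreseen in 7.2 and 9.4.

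The cost is a text amendment and a few minutes per affected family, with no new procedure or visit. The downsides are more recorded mild events and some readings not taken. The nNO comparison of means can absorb the losses shown above; the planned sensitivity estimate loses precision with each case reading not taken.
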